## Abstract

**Background:**

The number of interventions to support parents is growing. The level of evidence regarding these intervention varies. In this paper we describe a study that aims to assess the effectiveness of specific ‘elements’ within such parenting interventions for families with children up to 7 years. A naturalistic effect evaluation will be applied. Study questions are:
What is the exposure of parents to (elements of) parenting interventions in the daily practice of preventive youth health care?What are the associations between the exposure to (elements of) parenting interventions and outcomes in parents/children related to parenting and child development?

**Methods/design:**

Thousand parents/caregivers are recruited by preventive youth health care providers in the Netherlands. Measurements will be performed after inclusion and after 12-months follow up. Data regarding child/parent/caregiver characteristics, use of (parenting) interventions and care, and outcomes with regard to parenting skills, family functioning and child development will be collected. Outcomes will be compared between parents/children exposed and non-exposed to the (elements of) parenting interventions (adjusting for confounders).

**Discussion:**

We hypothesize that parents/caregivers with exposure to (elements of) parenting interventions show (relatively more) improvements in parenting outcomes. Results will support intervention selection/development, and support communities/professionals to select appropriate intervention-elements.

**Trial registration:**

Netherlands National Trial Register number NL7342. Date of registration: 05-November-2018, retrospectively registered.

## Background

Parental concerns are highly prevalent in the general population, and can therefore be considered as a usual aspect of parenting. In the Netherlands, studies report up to 50% of parents who have questions or concerns regarding the upbringing of their child [1–3]. Examples of topics of concern are child development, child health and diseases, children’s (difficult and disobedient) behavior, socio-emotional development of children and general parenting (skills) [1, 4]. Many parents feel the need to discuss their concerns with professionals or to receive other forms of parenting support [1].

Parenting support can be described as all activities, services, programs and interventions aimed at increasing parenting skills and improving the upbringing situation [1, 5]. There are various sources of parenting support, varying from informal support provided by one’s own social network, to services provided by semi-formal support sources (e.g. community-based voluntary sector organizations) or by formal support sources (e.g. typically involving statutory sector providers, or statutory and voluntary sector partnerships) [6]. Activities and interventions can be ‘universal’, aimed at all parents/caregivers, or ‘targeted’ at specific groups of parents who experience mild to severe levels of parenting problems or parenting stress, or who report behavior problems of their children [7].

Over the years, numerous parenting interventions have been developed with varying content, delivery settings, delivery techniques, types of families served and intended outcomes [8]. In general, there is considerable evidence that parenting interventions can have positive effects on a range of parent and child outcomes including parenting skills, parents’ self-efficacy and self-esteem, parent’s psychosocial health, parenting stress and child behavior [7–11].

The number of parenting interventions continues to grow. However, the level of the evidence regarding the effectiveness of the interventions varies. This makes it difficult for professionals to select the most appropriate and effective interventions. Moreover, studies investigating effectiveness of interventions are often focused on the interventions as a whole, while interventions generally consist of many elements. In order to better understand effects and mechanisms of behavior change interventions, it is important to identify which elements of the interventions contribute to the effects [12, 13]. These insights will be helpful for the development of new interventions and for intervention selection. Furthermore, it could enhance broader and more efficient implementation of existing interventions if these can be adapted to local needs and opportunities, and to the needs and strengths of the clients.

So, in addition to knowledge regarding the effectiveness of interventions, knowledge on the effectiveness of elements within the interventions is needed; but still scarce. Only a few meta-analyses that consider elements in parenting interventions have been carried out [8, 14, 15]. Therefore, the CIKEO consortium (Consortium Integration Knowledge promotion Effectiveness Of parenting interventions) aims to investigate effectiveness of elements of preventive parenting support. Knowledge is obtained from multiple sources: from published scientific research, professionals and families. In this paper we discuss the study protocol of a naturalistic effect evaluation within CIKEO to evaluate the effectiveness of parenting interventions in the daily practice of preventive youth health care (see below). The study aims to provide insight in both the effectiveness of interventions, as well as of elements of parenting support. For the latter, a relevant taxonomy of elements of parenting support will be applied (see below).

The CIKEO consortium is one of six consortia that are funded by ZonMw, the Netherlands Organization for Health Research and Development, in order to investigate the effectiveness of elements of all the interventions that are targeted to youth and families and that are registered in the national database of effective youth interventions in the Netherlands (Databank Effectieve Jeugdinterventies, website: www.nji.nl/nl/Databank/Databank-Effectieve-Jeugdinterventies)). Each consortium is focused on a different theme of interventions. The CIKEO consortium is a collaboration between partners of three Academic Collaborative Centrers (in Dutch: Academische Werkplaatsen) from the regions of Rotterdam, Leiden and Amsterdam in the Netherlands. Academic Collaborative Centers are local collaborations of academic institutions, public health services, municipal policy makers, elected officials and other relevant sectors. Knowledge exchange between these parties can stimulate the translation of scientific knowledge into practical products, services and facilities [16–18]. The executive partners of the CIKEO consortium are the Erasmus University Medical Center in Rotterdam, the Leiden University Medical Center in Leiden and the Verwey-Jonker Institute in Utrecht.

The CIKEO consortium started with an inventory study to give a brief up-to-date overview of the needs of parents, the use of preventive parenting interventions and the existing knowledge regarding the effectiveness of these interventions. The CIKEO consortium investigates parenting support using the approach of a naturalistic effect evaluation [19, 20] with a focus on the distinct elements within parenting interventions, and the ways the interventions are delivered. The elements of the parenting interventions are categorized according to the behavior change technique that are being applied, as proposed by Michie et al. [12]; this is referred to the “taxonomy of Michie” [12].

In this paper, the design and methods of the naturalistic effect evaluation [19] of the CIKEO consortium will be described in detail. This is a prospective cohort study among parents with children up to 7 years. The objectives of the study are:
To study the exposure of parents to (elements of) parenting interventions and other types of parenting support in the daily practice of the preventive youth health care.To investigate the associations between the exposure to (elements of) parenting interventions and other types of parenting support and outcomes in parents and children related to parenting and child development (see below).

The hypothesis is that parents/caregivers who receive (elements of) parenting support during the follow-up period will show (relatively more) improvements in parenting skills, family functioning and child development compared to comparable parents/children who did not receive parenting interventions.

## Methods/Design

### Preventive youth health care in the Netherlands

The preventive youth health care is a system for monitoring children’s health and development, and for providing health promotion and disease prevention [21]. It is offered nation-wide and free of charge, independent of insurance status. Participation is voluntary. From birth onwards, parents are frequently invited with their child to visit preventive youth health care centers. The attendance rate is about 95%. During these visits, the growth, development, health and well-being of the child are assessed [21–23]. Additionally, youth health care professionals provide information about the development and upbringing of children and promote a stimulating pedagogical climate. They aim to identify child behavior problems or parenting problems in an early stage and organize help when needed. The youth health care professionals can provide pedagogical counseling or they can direct parents and families to parenting interventions offered by themselves or other providers [1, 24]. In this way, youth health care providers can serve as link with specialized services; they are the frontline services for a broad range of questions [24]. Municipalities are responsible for the preventive youth health care and facilitate a suitable offer of preventive services and coordinate the collaboration between these services [1, 24].

### Parenting interventions and parenting support

For this study, parenting interventions of interest are defined as follows: Interventions for parents with children aged up to 7 years old, targeted at improving parenting skills, parental competences, child development and behavior of the child. The interventions in this study have the aim to prevent (parenting) problems to arise or to intervene with high risk groups or in families with mild problems, to prevent problem from becoming more severe. Interventions for treatment of severe or clinical problems, are beyond the scope of this study.

The CIKEO consortium will study a selection of 21 preventive interventions (see Additional file 1), based on national professional youth health care guidelines [1] and on inclusion within the Dutch national Database of Effective Youth Interventions (in Dutch: Databank Effectieve Jeugdinterventies) of the Netherlands Youth Institute (www.nji.nl/nl/Databank/Databank-Effectieve-Jeugdinterventies) in the year of 2017. In order to be eligible for inclusion in this database, interventions should have a structured and goal-oriented approach, aimed at children and youngsters aged -9 months to 24 years, their caregivers and or parenting environment. The intervention should be carried out in the Netherlands and should have an accessible manual in Dutch language. At least a limited process evaluation should be available. Finally, the intervention should be submitted by the owner or licensee. Once these criteria are met, the intervention is further assessed by an independent committee of national experts to be accepted in the database and to be classified into one of four categories differing in indications of effectiveness [25].

Of the CIKEO selection of 21 interventions, 19 interventions are relevant to the population of this study; parents/caregivers of children up to 7 years old (see Additional file 1). In addition, this study also includes a) practice-based interventions that are not registered in the database of effective youth interventions, b) consultations regarding parenting, c) informal types of parenting support (for example parenting books, websites) and d) regular monitoring visits to the youth health care centers.

### Study design

The design is a naturalistic effect evaluation [19]. It is an observational prospective cohort study with a baseline and follow-up measurement (12 months after inclusion). The total study sample will consist of parents with various levels of parenting problems and concerns. Both at baseline and at follow-up, all participating parents/caregivers will be asked to complete a questionnaire. There are no separate intervention and control groups in this study. The exposure of parents/caregivers to (elements of) parenting support during the follow-up period will be established by the follow-up questionnaire and from electronic files of the youth health care organizations (only with permission by the study participants, see below). By comparing the outcome measures between baseline and follow-up measurements, we aim to investigate which interventions and/or elements of parenting support are associated with a relative decrease in problems and improvement in positive outcome measures in parents and their children.

Data collection started in October 2017 and will continue until April 2020.

### Ethics

The research proposal was reviewed by the Medical Ethics Committee of the Erasmus Medical Center, Rotterdam. Based on their review, the Committee concluded that the rules laid down in the Dutch Medical Research Involving Human Subjects Act (also known by the Dutch abbreviation WMO, in full ‘Wet Medisch-wetenschappelijk Onderzoek met mensen’) do not apply to this research proposal (proposal number MEC-2017-432), and gave permission to conduct this study at Erasmus Medical Center and to submit the results for publication in a scientific journal in the future (Letter NL/sl/321518; 24/07/2017). All participants in the study will provide written informed consent.

### Participants and recruitment

We aim to include a total of net 1000 families in the cohort study. Recruitment will take place in two parts.

Part A) A sample of net 800 parents/caregivers of children aged 0–7 year will be included by two regional preventive youth health care providers (CJG Rijnmond and Rivas Zorggroep) in the regions of Rotterdam and Dordrecht, the Netherlands. These preventive youth health care organizations will inform a sample of parents/caregivers of children aged between 15 and 21 months and children aged 5 or 6 years (second grade of primary school) from their registries about the study, and invite them to participate. All invited parents/caregivers will receive project information, an informed consent form and a baseline questionnaire. Parents/caregivers who are willing to participate are requested to return the completed baseline questionnaire and the signed informed consent form to the researchers in a pre-paid envelope or via internet. All parents/caregivers who provide informed consent and a completed questionnaire are enrolled in the study.

Part B) Part B concerns an opportunity sample of net 200 parents/caregivers of children aged 0–7 year who will participate in a parenting intervention during the follow-up period. Preventive youth health care organizations and other providers of parenting support are informed about the study. They are asked to inform parents who participate in interventions about the study. The procedure regarding study information, informed consent and data collection is similar as for the parents in part A. In addition, participants are recruited directly through advertisements on websites about parenting. They will be directed to the digital version of the project information, the informed consent form and the questionnaire. All parents/caregivers who provide informed consent and a completed questionnaire are enrolled in the study.

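### Part B is selected on intended intervention use and pooled with the registry sample, so pooled exposure overstates daily practice and recruitment route is tied to exposure in the any-support contrast

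*Protocol article*

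**What the plan says.** The section Participants and recruitment sets one target for the whole study: "We aim to include a total of net 1000 families in the cohort study". It fills that target by two routes.

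- **Part A:** "A sample of net 800 parents/caregivers of children aged 0–7 year will be included by two regional preventive youth health care providers". Those invited are parents of "children aged between 15 and 21 months and children aged 5 or 6 years (second grade of primary school) from their registries".
- **Part B:** an "opportunity sample of net 200 parents/caregivers of children aged 0–7 year who will participate in a parenting intervention during the follow-up period". Youth health care organisations and other support providers pass on the invitation: "They are asked to inform parents who participate in interventions about the study". A further route is open: "In addition, participants are recruited directly through advertisements on websites about parenting".

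In both parts, consent and a completed questionnaire are enough for enrolment.

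Study design then states: "There are no separate intervention and control groups in this study". Exposure is established later, from the follow-up questionnaire and, with permission, from electronic files. Data management and statistical analysis uses a yes/no exposure as the independent variable. Baseline values and potential confounders enter in additional models, with demographic characteristics as the example. Power considerations works on 600 completers from both parts together, half of them exposed. Recruitment part appears in none of these sections as a stratum, covariate or sensitivity analysis.

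**The concern.** The two study questions need different things from the sample, and pooling the parts without distinction harms both.

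Question 1 in the Abstract asks how far parents are exposed to parenting interventions in the daily practice of preventive youth health care. One fifth of the cohort is chosen because it intends to take an intervention. A prevalence over all 1000 is then partly a product of the recruitment quota.

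Question 2 compares exposed with unexposed parents, and the hypothesis in the Background speaks of comparable parents. For the contrast of any support against none, Part B supplies exposed parents and few or no unexposed ones. The Discussion says that recruitment through support providers is meant to reach parents at risk of parenting problems. The article thus expects this route to bring in a different risk level, and it does so almost entirely on the exposed side. Any difference between the routes that the covariates do not capture is read as an effect of support.

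**Working it through.** **Inputs from the article.** Part A 800 and Part B 200 (Participants and recruitment). Loss 40%, 600 completers, 50% (300) exposed, two-sided alpha 0.05, power 0.80, 25 clusters of 24, intra-class correlation 0.02, detectable difference 0.27 SD, meaningful difference 0.5 SD (Power considerations).

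**1. The article's own figure.** Design effect = 1 + (24 − 1) × 0.02 = 1.46. Detectable difference = (1.960 + 0.842) × √1.46 × √(1/300 + 1/300) = 0.276 SD. The stated 0.27 is this value cut rather than rounded, which does not matter here. The calculation is on the pooled 300 against 300.

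**2. Question 1.** Assume equal loss in both parts: 800 × 0.6 = 480 and 200 × 0.6 = 120 completers. If all of Part B is exposed, Part A must supply 300 − 120 = 180 exposed, and 180/480 = 37.5%. Pooling adds 12.5 percentage points.

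The exposed share of Part B is an assumption, so it is varied with the pooled share held at 50%:

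| Part B exposed | Part A exposed | Added by pooling |
|---|---|---|
| 100% | (300 − 120)/480 = 37.5% | 12.5 points |
| 90% | (300 − 108)/480 = 40% | 10 points |
| 80% | (300 − 96)/480 = 42.5% | 7.5 points |
| 70% | (300 − 84)/480 = 45% | 5 points |

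Unequal loss also moves the figure. Keep 600 completers and a fully exposed Part B. Loss of 45% in A and 20% in B gives (300 − 160)/440 = 31.8% in Part A. Loss of 35% in A and 60% in B gives (300 − 80)/520 = 42.3%. The direction is upward whenever Part B is more exposed than Part A.

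**3. Question 2, any support against none.** Let d be the difference between Part B and Part A in the outcome, in SD, that is not caused by support and not removed by adjustment. The shift in the contrast is d × (share of Part B among the exposed − share of Part B among the unexposed).

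- Part B 100% exposed: 120/300 − 0/300 = 0.40, so the shift is 0.4d.
- Part B 80% exposed: 96/300 − 24/300 = 0.24, so the shift is 0.24d.

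The article gives no value for d. At the 0.4d limit, d = 0.25 gives 0.10 SD, d = 0.5 gives 0.20 SD, and d = 0.27/0.4 = 0.675 gives the whole stated detectable difference. Under the unequal-loss cases above, Part B's share of the exposed runs from 80/300 = 27% to 160/300 = 53%, and the multiplier moves with it.

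**4. Cost of accounting for recruitment part.** If Part B is fully exposed, a model with recruitment part as a covariate takes its any-support contrast from Part A alone, 180 against 300. Detectable difference = 2.802 × √1.46 × √(1/180 + 1/300) = 0.319 SD. The same value follows from the correlation of 0.5 between part and exposure: 0.276 × √(1/(1 − 0.25)) = 0.319. Power at 0.27 SD is 0.66.

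**The case against.** The best defence is that enriching a cohort with exposed and at-risk families is a legitimate and disclosed choice, and that the plan has tools for the consequences. Baseline outcomes and an open-ended list of confounders enter additional models. Child age, distress, social support, life events and prior use of care are all collected. The Discussion concedes residual confounding. The article also never says that question 1 will be reported over both parts combined, and analysis sets may be set out in a fuller document.

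Part of this stands. Pooling for question 1 is inferred from the single cohort, the single exposure variable and the pooled power basis. The shift of 0.4d applies only to what adjustment leaves behind. But the general remark on residual confounding does not recognise that recruitment route is tied to exposure by the selection rule, and adjustment removes only what is measured.

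Four stronger readings are tempting, and the documents do not support them.

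- *Part B is wholly exposed, so no unexposed parent comes from it.* Intended participation is a selection rule that enrolment does not verify, and parents who never attend would later be classed as unexposed. For a single element, Part B parents whose intervention lacks that element are unexposed, so the imbalance belongs to the any-support contrast.
- *The bias is 0.20 SD.* That needs an assumed d of 0.5, for which the article has no source.
- *Most Part B children have no counterpart of their age in Part A.* Part A does invite only two age bands, but Part B's age distribution is not given, and child demographics are among the planned covariates. Adjustment outside those bands would nevertheless be extrapolation.
- *Part B baselines are taken during treatment.* The invitation to parents who participate makes this possible, but the stated criterion is future participation.

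**Conclusion.** The point holds for two uses of the data: pooled exposure prevalence, and the any-support contrast. For the first, pooling overstates exposure by 12.5 percentage points if Part B is fully exposed, and by 5 to 10 points if 70% to 90% of it is. This assumes equal 40% loss and the article's 50% pooled exposure. For the second, up to 40% of the exposed and few or none of the unexposed come from Part B under the same assumptions, which gives a shift of up to 0.4d for any route difference d left after adjustment. The size of d is unknown, so the plan carries an exposure to bias of unknown size, not a demonstrated bias. Comparisons of elements among supported parents are not open to this criticism in the same way.

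**What to change.** - **Question 1:** estimate exposure prevalence from Part A only, or report it separately by part.
- **Question 2, any support:** include recruitment part as a stratum or covariate, and report the Part A contrast alongside the pooled one. Which of the two leads is a judgement, because restricting to Part A gives up about 120 of 300 exposed parents and does not remove confounding by indication.
- **Part B:** use it mainly to compare elements among supported parents. Flag parents whose intervention began before the baseline questionnaire.
- **Power considerations:** restate the detectable difference for the any-support contrast as about 0.32 SD (about 180 against 300) in place of 0.27 SD (0.276 recomputed).

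No extra recruitment is needed. The changes are a few sentences of analysis text and the start date of each Part B intervention, from the follow-up questionnaire or, where permitted, the electronic files. The real cost is precision, and 0.32 SD still lies below the 0.5 SD that the article calls meaningful.

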### Data collection and measurements

Data will be collected through questionnaires that will be filled out by the primary caregiver of the child at baseline (time of inclusion) and after a follow-up period of twelve months. The questionnaires can be completed on paper or digital through a secured website. All questionnaires consist of valid and evidence-based instruments; details are described below. In the questionnaire, the participants can indicate whether they want support by a professional caregiver; if so, they will be referred accordingly.

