### Received parenting support and use of care

In the baseline questionnaire, the use of various types of care in the previous year by the parent/caregiver, child and/or other children in the family will be assessed, including the general practitioner, medical specialists, psychological help, parenting support and other types of care (18 items). Furthermore, we include 3 items regarding visits to the youth health care centers.

In the follow-up measurement, the use of care will be assessed similarly as in the baseline questionnaire. Additionally, 3 items are included to assess whether parents/caregivers had questions or concerns regarding the upbringing of their child, whether they had been in need for parenting support and whether they have received parenting support during the follow-up period. Visits to youth health care centers, participation in parenting interventions, visits to parenting lectures and other types of parenting support during the last year are assessed by 20 items, including items considering the duration, frequency, character, content and the parents’/caregivers’ appreciation of the received parenting support. Additionally, when available and with permission of participants, data on received parenting support and care regarding parenting during the follow-up period will be collected from electronic files of preventive youth health care organizations.

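### Part B's provider route can enrol parents who have already started an intervention, so their baseline may already contain part of the effect

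*Protocol article*

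**What the plan says.** All references are to the Protocol article.

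- **Participants and recruitment.** Part B is an opportunity sample of net 200 parents "who will participate in a parenting intervention during the follow-up period". Of providers of parenting support it says: "They are asked to inform parents who participate in interventions about the study". A second route is advertising on parenting websites. Entry is then stated as: "All parents/caregivers who provide informed consent and a completed questionnaire are enrolled in the study".
- **Data collection and measurements.** The primary caregiver fills out questionnaires "at baseline (time of inclusion) and after a follow-up period of twelve months". Baseline is therefore tied to inclusion, not to the start of an intervention.
- **Study design.** "The exposure of parents/caregivers to (elements of) parenting support during the follow-up period will be established by the follow-up questionnaire", and also from electronic files where the parent permits. The interventions and elements linked to improvement are to be found this way: "By comparing the outcome measures between baseline and follow-up measurements".
- **Data management and statistical analysis.** Exposure is coded yes or no. The first regression has exposure as its independent variable. Baseline values and potential confounders come in only in additional models.
- **Received parenting support and use of care.** The baseline questionnaire covers "the use of various types of care in the previous year by the parent/caregiver", and parenting support is one of the types listed. The follow-up questionnaire asks about duration and frequency of support, among other things.

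**The concern.** The definition of Part B looks forward from inclusion, while the instruction to providers is in the present tense. A parent in the middle of a course satisfies every rule that is stated: participation continues into follow-up, consent is given, and a questionnaire is completed. That parent's baseline is a mid-course measurement.

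The study looks for relative improvement from baseline to follow-up. Benefit already gained at inclusion cannot appear as improvement afterwards. A change score removes it in full, and a model with baseline as covariate removes it in proportion to the baseline slope. If early gains are beneficial, both estimates move toward no effect. In a non-randomized cohort the adjusted models carry most of the weight, because the unadjusted contrast is open to confounding. Part B also exists to supply exposed families, so the problem sits in the group recruited to show the effect.

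**Working it through.** **1. The plan's own figure.** Power considerations states 300 exposed and 300 unexposed completers, two-sided alpha 0.05, power 0.80, clusters of 24 and an intra-class correlation of 0.02.

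- Design effect = 1 + (24 - 1) x 0.02 = 1.46.
- Effective number per group = 300 / 1.46 = 205.5.
- Detectable difference = (1.960 + 0.842) x sqrt(2 / 205.5) = 0.276 SD.
- Power at the stated 0.27 SD = 0.78.

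The stated 0.27 SD is reproduced closely enough. It refers to a difference at follow-up with no baseline term, and the present point does not depend on it.

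**2. Part B's share of the exposed.** The inputs from the document are 200 parents in Part B, 40% drop-out and 300 exposed completers. Assume equal drop-out in both parts and that every Part B completer is exposed.

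- Part B completers = 200 x 0.6 = 120.
- Share of exposed = 120 / 300 = 0.40.

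**3. Shrinkage.** Three quantities are assumed, because the document gives none of them:

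- q: share of Part B that had started before baseline
- f: share of their effect already present at baseline
- b: weight on baseline (1.0 for a change score, lower for a regression slope)

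Assume also that the effect reached by follow-up is the same for early starters and others. Then shrinkage within Part B = q x f x b, and pooled shrinkage = 0.40 x q x f x b.

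| q | f | b | Within Part B | Pooled | A true 0.27 SD becomes |
|---|---|---|---|---|---|
| 0.25 | 0.25 | 0.6 | 3.75% | 1.5% | 0.266 |
| 0.50 | 0.50 | 0.6 | 15% | 6% | 0.254 |
| 0.50 | 0.50 | 1.0 | 25% | 10% | 0.243 |
| 1.00 | 0.50 | 1.0 | 50% | 20% | 0.216 |

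Widening the ranges to f = 0.75 and b = 0.5 gives pooled shrinkage from 0.40 x 0.25 x 0.25 x 0.5 = 1.25% to 0.40 x 1.00 x 0.75 x 1.0 = 30%.

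**4. What that means for power.** This is illustrative only, because it borrows the standard error of the unadjusted contrast. From 0.78 at 0.27 SD, power falls to about 0.69 with 10% shrinkage and 0.59 with 20%. A true effect of 0.5 SD, which the plan calls meaningful, would shrink to 0.40 SD at 20%, and power would still be about 0.98.

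**5. Where the mechanism does not act.** In the first regression, and in the follow-up difference used for the power statement, nothing is subtracted, so pre-baseline gain stays in the estimate.

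**The case against.** The strongest reply is that the definition already settles the matter. Part B is stated to be parents who will participate during follow-up. The instruction to providers can be read as a generic present tense inside that definition. The enrolment sentence does not cancel the definition, since the same sentence closes Part A without cancelling its age groups. Website recruits need not be in an intervention at all. This stands to the extent that the document nowhere says parents have already started. It does not close the gap, because an ongoing course also fits participation during follow-up and no stated condition excludes it.

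A second reply is that an article may leave out item-level detail. The 20 follow-up items cover duration and frequency, and a start date may be among them. That is fair, so the absence of a start date cannot be asserted as a fact about the questionnaires. What can be said is that no stated rule uses timing to separate new from continuing users.

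A reader might go further and infer that the comparison group is contaminated, because parents whose support ended before baseline count as unexposed. If 20% of them kept half the benefit, the unadjusted contrast would shrink by 0.20 x 0.5 = 10%. The document does not support calling this an error. Exposure is defined as support during follow-up, the baseline-adjusted models deal with retained benefit at least in part, and the confounder list is open-ended. Both figures in that sum are also assumed.

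A reader might also infer that every effect estimate is diluted. The unadjusted models are not diluted by this route.

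**Conclusion.** The point holds in a limited form. The stated recruitment route does not secure the stated definition of Part B, and a baseline taken after exposure began is compatible with every rule given. For such parents, the baseline-to-follow-up comparison and the baseline-adjusted models understate a beneficial effect.

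Only 200, 40% and 300 come from the document. Under the assumptions shown, the pooled estimate shrinks by about 1.5-20%, and the Part B estimate by about 4-50%. That range runs from trivial to material, so the true size is unknown until start dates are seen. It is a worthwhile, low-cost improvement and not a flaw that invalidates the study. The claim that Part B families have in fact already started treatment goes beyond the text.

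**What to change.** 1. In Participants and recruitment, reconcile the forward-looking definition with the present-tense instruction. Ask that the Part B baseline questionnaire be completed before the first session where possible, for provider and website recruits alike.
2. Record the intervention and its first-session date. For parents already enrolled (data collection began in October 2017), take the date from the follow-up questionnaire or, where available, the electronic files.
3. Flag parents who had started before baseline and report a sensitivity analysis without them.
4. In Data management and statistical analysis, name prior-year parenting support as a covariate in the adjusted model. It is already collected at baseline. The care items also cover other children in the family, so it is an imperfect marker.

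**Cost.** There is one extra item, some start dates will be recalled or missing, and the interval in the sensitivity analysis is wider. If 25% of Part B had started, 30 of 300 exposed completers drop out of it, and the standard error rises by sqrt[(1/270 + 1/300) / (2/300)] = 1.03. If all had started, 120 drop out, and the factor is sqrt[(1/180 + 1/300) / (2/300)] = 1.15. Both assume an unchanged design effect. Because of that possible loss, a sensitivity analysis is preferable to excluding early starters from the main analysis.
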